**Sample size calculation**

Group size was determined to allow for the detection of large effect sizes with an α-error probability of p≤ 0.05 and a β-error probability of p≤ 0.20.

**Time schedule**

July 2009: preparation of training materials

August 2009 – May 2010: recruitment and examination of participants

June – July 2010: data analysis and research report

**Time flow:**

After inclusion participants receive in group meetings an instruction in the application of floss to reach a standardized interdental hygiene as far as possible. These skills will be checked several times within the next two weeks. Afterwards all participants receive a professional tooth cleaning and the instruction of one of the three tooth brushing techniques. Dependent variables will be assessed two, six, twelve and twenty-eight weeks after this intervention. All participants receive standardized tooth brushes, toothpaste and floss for the investigation period and they will be encouraged to use these for their daily oral hygiene. After fourteen weeks the materials will be changed and all participants receive new materials. Therefore the participants bring back their old materials.

**Privacy of study subjects**

Input of questionnaire data takes place in a pseudonymized form and they will be saved locked and separated from personal data.

**Participants safety**

Participants are not at risk in this study.

**Quality management**

All examination will be performed by calibrated examiners and a standardized evaluation of the validated questionnaires will be provided.

**Guidelines**

CONSORT-Guidelines.

**Publication**

An international publication of results is planned.

**Publication of the trial protocol**

A publication of the trial protocol and registering the study respectively is not planned yet.

**List of Amendments**

1.) Presentations of the Stillman technique turned out to be very similar to those of the Bass technique. Indeed, pictures and videos of the two techniques were hardly to differentiate. We thus decided to omit the Stillman technique and to inculde a control group instead, which was taught only basics of tooth brushing and no specific brushing technique.

2.) Data on oral hygiene (dark blue staining prior to tooth brushing) were excluded from analyses due to a misunderstanding when assessing oral hygiene. While maufacturer proposes to assess all blue staining in order to assess older deposits we assessed dark blue staining, only. Since gingivitis is considered another good clinical indicator for oral hygiene we focused this parameter instead.

3.) Data of the two-week-assessment point were omitted from analyses as this point in time turned out to be too close to the professional tooth cleaning with nearly no bleeding and very low degree of staining after tooth brushing (indeed, the loweset observed in all groups throughout the study) both obviously reflecting the favorable after-effects of the professional tooth cleaning rather than oral hygiene activities of the participants.

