**Comparison of brushing techniques- a multidisciplinary, randomised study teaching oral hygiene skills**

**Trial Protocol**

**(Translation of the original German protocol plus list of amendments)**

**Aim of the Study**

The aim of the study is a longitudinal controlled comparison of effectiveness of different brushing techniques. Three of the best known brushing techniques (Stillman, Fones and modified Bass) should be compared with each other and a control group. When planning such a study one has to take into account, that you need more than only dental experts to teach a brushing technique. Furthermore it is necessary to implement knowledge of movement sciences such as best teaching of fine motor motion sequence. In addition it requires psychological expertise to teach information in a way that it can be optimal processed, remembered and transformed and motivational aspects to support the application in everyday life. The present study will follow this approach to connect these three disciplines. A PowerPoint presentation will be worked out for every technique (Stillman, Fones and Bass) taking into account in all presentations knowledge of dentistry, movement sciences and psychology. The presentations are constructed in a way that participants are able to get through the presentation by themselves and to follow them in his/her own tempo. Additionally, they are able to follow single training steps in a mirror placed nearby. Another aim of this study is to evaluate the success of teaching these techniques with the help of clinical parameters in the following period. An equal focus is placed on oral hygiene skills, actual oral hygiene and oral health of the participants.

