**Study Design**

After inclusion participants receive in group meetings an instruction in the application of floss to reach a standardized interdental hygiene as far as possible. These skills will be checked several times within the next two weeks. Afterwards all participants receive a professional tooth cleaning and the instruction of one of the three tooth brushing techniques. Dependent variables will be assessed two, six, twelve and twenty-eight weeks after this intervention. All participants receive standardized tooth brushes, toothpaste and floss for the investigation period and they will be encouraged to use these for their daily oral hygiene. After fourteen weeks the materials will be changed and all participants receive new materials. Therefore the participants bring back their old materials.

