**Primary outcome measure**

Primary outcome measure is oral health 28 weeks after intervention.

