**Secondary outcome measure**

Secondary outcome measures are oral hygiene skills at 28 weeks and on the other appointments and oral health on the other appointments.

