**Biometrical/Statistical Analyses**

Primary outcome measure is oral health 28 weeks after intervention. Secondary outcome measures are oral hygiene skills and oral hygiene at 28 weeks and on the other appointments and oral health on the other appointments. Percentage of unstained sites MPI and TQHI and percentage of sites without bleeding are assessed. The inference-statistical analyses shall be made by [name]. [name].

Statistical data analyses will be conveyed with analysis of variance. Additionally exploratory analyses follow to investigate the effect sizes of group differences.

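### Amendment 3 drops the planned two-week results for two secondary outcomes because of the levels observed there; they should be reported and the omission labelled post hoc

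*Protocol*

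**What the plan says.** The Study Design section, repeated under Time flow, sets the visits: "Dependent variables will be assessed two, six, twelve and twenty-eight weeks after this intervention". The same paragraph gives every participant a professional cleaning together with the brushing instruction, before the first of these visits.

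The Secondary outcome measure section reads: "Secondary outcome measures are oral hygiene skills at 28 weeks and on the other appointments and oral health on the other appointments". Biometrical/Statistical Analyses has a slightly wider list: "Secondary outcome measures are oral hygiene skills and oral hygiene at 28 weeks and on the other appointments and oral health on the other appointments". Under either version, week-2 skills and week-2 oral health are planned secondary outcomes. The primary outcome is separate: "Primary outcome measure is oral health 28 weeks after intervention".

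Item 3 of the List of Amendments changes this: "Data of the two-week-assessment point were omitted from analyses as this point in time turned out to be too close" to the cleaning. The support offered is that there was almost no bleeding at week 2 and very little stain left after brushing, the staining being "the loweset observed in all groups throughout the study". The amendment attributes both findings to the cleaning rather than to what participants did. The list carries no dates.

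**The concern.** A planned visit is removed, and the justification given is what the data at that visit looked like. The body of the protocol contains no rule for dropping a visit. When a visit is dropped after its values are known, the reader sees a time course chosen with results in view and cannot judge whether the omitted visit would have altered the picture.

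The Aim of the Study section adds weight: "Another aim of this study is to evaluate the success of teaching these techniques with the help of clinical parameters in the following period". It places equal focus on skills, actual oral hygiene and oral health. Week 2 is the first time skills are measured after teaching. Without it, a group difference that is absent at week 6 could mean that the technique was never learned or that it was learned and then faded.

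**Working it through.** No sample size formula or test statistic is involved. The check compares the sections and counts results.

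**1. Was week 2 planned?** Yes. Study Design lists it, and both outcome sections include the interim appointments without exception.

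**2. What was new when the visit was dropped?**
- The order of cleaning, instruction and first assessment, and the two-week interval, stood in the original design.
- The cleaning was given to all participants.
- The observed levels were new. To know that week-2 staining was "the loweset observed in all groups throughout the study", one needs staining from later visits, summarised by group. By the time the amendment was written, outcome levels by group had therefore been seen.

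**3. Does the reason justify removal?** A cleaning common to all arms can push values towards a floor and so compress a group difference. By itself it does not create a false one. That is a reason to read week 2 with caution. It is not a reason to withhold it. Also, skills are scored directly after participants brush as well as they can, so it is not self-evident that the score reflects only a cleaning two weeks earlier. The week-2 comparison by arm is the evidence that bears on this.

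**4. How much is removed?**

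| Outcome | Secondary results planned | Left after Amendments 2 and 3 |
|---|---|---|
| Skills | weeks 2, 6, 12, 28 = 4 | weeks 6, 12, 28 = 3 |
| Oral health (bleeding) | weeks 2, 6, 12 = 3 | weeks 6, 12 = 2 |
| Total | 7 | 5 |

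Amendment 3 thus removes 2 of 7, or 1 of the 3 interim visits. Starting from the wider list in Biometrical/Statistical Analyses, the count is 4 + 4 + 3 = 11. Amendment 2 removes the 4 oral hygiene results (11 − 4 = 7), and Amendment 3 removes 2 more (7 − 2 = 5). The end point is the same.

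**5. Could it alter a longitudinal result?** The protocol says only that analysis of variance will be used. As an illustration, assume a group difference *d* at each of weeks 6, 12 and 28 and none at week 2 because of a floor. The average difference over visits is (*d* + *d* + *d*)/3 = *d* without week 2, and (0 + *d* + *d* + *d*)/4 = 0.75*d* with it. The choice can therefore matter for an effect pooled over visits. It does not enter separate comparisons at weeks 6, 12 or 28.

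**The case against.** The omission is openly declared with a plausible reason. The primary outcome is untouched, and skills and bleeding are still measured at several later visits. Week 6 is also a measurement after teaching, and the aim section does not name week 2. All of this stands and limits the weight of the point.

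The remark about the whole study is a parenthesis in an undated list. It may have been added as support when the list was written and need not have triggered the decision. That is fair as to sequence. But the main clause itself argues from observed levels, and the missing date is part of the problem.

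A floored visit can dilute a pooled group effect, as the illustration shows. That supports presenting an analysis without week 2, but not leaving the week-2 results unreported.

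Two stronger readings are tempting, and the document supports neither:
- **A reader might infer that the error rates of the remaining secondary results can no longer be interpreted.** The stated ground is a low level in every group, not a group contrast. Choosing visits by overall level does not in itself inflate the false-positive rate of separate comparisons at the other visits. The protocol also states no error-rate control across secondary outcomes that the omission would break.
- **A reader might infer that the visit was dropped to favour one technique.** Nothing in the amendment says that a week-2 group difference had been examined or used.

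**Conclusion.** The point holds as a matter of selective reporting within the secondary outcomes. Amendment 3 is a post hoc, undated omission based on observed outcome levels. It takes out 2 of 7 secondary outcome-by-visit results and the first measurement after teaching. The 28-week primary outcome stands as planned. The point should be fixed, but it does not undermine the trial's main comparison.

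This rests on two assumptions. First, the control group introduced by Amendment 1 received the same cleaning; the Study Design text covers all participants, and Amendment 3 reports low values in all groups. Second, the week-2 data were collected and kept, as the amendment's description of them implies. Whether group differences had been looked at before the decision cannot be determined from the document.

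**What to change.** In Amendment 3, replace the exclusion with the following:

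- Report week-2 skills and bleeding by arm with 95% confidence intervals, and add a remark on the after-effect of cleaning and the possible floor.
- Label any longitudinal analysis that leaves out week 2 as post hoc, and show the result with week 2 alongside it.
- State when the decision was made and what was known by group at that time.

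A mixed model with unstructured covariance over all four visits is one option. It is not required, and it may fit poorly if there is almost no variation in bleeding at week 2.

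The cost is revised amendment wording and one more column in the tables, since the data exist. The downside is that a pooled group effect may look smaller in the analysis that includes week 2; showing both versions lets the reader see why.
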